### 2.5. Randomization and Allocation Concealment

After registration, the participants will be randomized to Group 1, Group 2, Group 3, or Group 4. Group 1 will receive verum acupuncture; Group 2 will receive Park Sham Device acupuncture; Group 3 will receive Streitberger's needle acupuncture; and Group 4 will receive insertion- and removal-type acupuncture. In this allocation, the stratified-block randomization will be conducted by an independent CRC. The stratification is performed according to whether there is a sensory disturbance of the affected limb (1: no sensory disturbance; 2: sensory disturbance). Block lengths are eight. Random assignment will be conducted by computer-based randomization. The block random function of R software (version 3.1.2) will be used to generate a random number. The assignment probability of the treatment group and the three control groups is 1 : 1 : 1 : 1. For allocation concealment, an independent CRC places the random assignment code in an impermeable envelope and seals it, and it is then delivered to the practitioner. The practitioner will open the random assignment envelope in front of the participant and assign the participant. After that, practitioners will keep the opened envelopes with themselves.

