### 2.10. Sample Size Calculation

This study was not intended to evaluate the effectiveness of acupuncture treatment but rather to evaluate the suitability of various sham devices. Therefore, we did not follow the general method for obtaining the sample size. The target number of participants in this study was selected on the basis of the number of participants in the previous study [14], which was a sham acupuncture comparison study conducted in healthy individuals [14]. In the previous study, the participants were divided into verum acupuncture, Park Sham Device, Needle + Foam, Insertion and Removal, Real + Park Sham device, Real + Needle + Foam, and Real + Insertion and Removal groups. Twenty-two participants per group were recruited. Therefore, on the basis of this, we decided to recruit at least 22 participants for each group and to recruit 90 stroke patients considering withdrawal during the trial.

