### 2.11. Statistical Analysis

Hypothesis to be tested in this study is that the certain sham device will reveal the most similar sensation to verum acupuncture in the affected limb of stroke patients. Primary outcome of this study is Bang's blinding index in each group. The value of Bang's blinding index of each sham acupuncture device will be calculated by comparison with the verum acupuncture group. This statistical process will be based on Bang's previous study, published in 2004 [18]. In secondary outcome analysis, the values of “Discomfort caused by acupuncture therapy” five questions and MASS index will be compared by ANOVA. In baseline characteristics, categorial variables will be compared by a chi-square test and continuous variables will be compared by ANOVA. A comparative analysis of the frequency of patients with sensory disturbances by each group will evaluate whether stratification assignments have been made properly. In subgroup analysis, we will compare the values of primary and secondary outcomes in patients with sensory disturbances. Patients with sensory disturbances are defined as patients who complaint sensory disturbances such as numbness, hypesthesia, or paraesthesia in affected limbs. In this study, sensitivity analysis will not be performed. A 5% significance level will be used. Study data will be analyzed using the Statistical Package for the Social Sciences (SPSS) software, version 16.0, for Windows and Microsoft Excel 2010 for windows by a blinded statistician.

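### Comparing sensory-disturbance frequency between groups gives almost no evidence that stratified assignment was carried out; a reconciliation against the randomisation list would

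*Protocol article*

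**What the plan says.** Section 2.5 of the protocol article sets the design: "The stratification is performed according to whether there is a sensory disturbance of the affected limb", with two levels. It adds "Block lengths are eight" and "The assignment probability of the treatment group and the three control groups is 1 : 1 : 1 : 1". Codes are sealed in envelopes by an independent coordinator and delivered to the practitioner, who opens them and keeps them afterwards.

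Section 2.11 then describes the check: "A comparative analysis of the frequency of patients with sensory disturbances by each group will evaluate whether stratification assignments have been made properly". The sentence just before it says that, for baseline characteristics, "categorial variables will be compared by a chi-square test". The same section states "A 5% significance level will be used". It defines the factor by patient report: "Patients with sensory disturbances are defined as patients who complaint sensory disturbances such as numbness, hypesthesia, or paraesthesia in affected limbs". No other criterion for proper stratification is given.

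On size, Section 2.10 says "we decided to recruit at least 22 participants for each group and to recruit 90 stroke patients considering withdrawal during the trial".

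**The concern.** The check compares the frequency of sensory disturbance across the four groups. On the natural reading this is a chi-square test of a 4 x 2 table, whose null hypothesis is that group is independent of sensory status. That null is true under correct stratification. It is equally true if the stratification factor was ignored and patients were simply randomised. A test cannot separate two situations that both satisfy its null hypothesis.

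Sensory disturbance is the only stratification factor and defines the only planned subgroup. Followed as written, the trial could report that stratified assignment was proper on a result it would very probably have seen anyway.

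**Working it through.** **Inputs.** N = 90 (Section 2.10: 4 x 22 = 88, plus 2 for withdrawal). Four arms at 1:1:1:1 and blocks of eight within two strata (Section 2.5). Chi-square at 5% (Section 2.11). A 4 x 2 table has 3 degrees of freedom, so the critical value is 7.815. The protocol gives no prevalence of sensory disturbance; 30%, 50% and 70% are assumed unless stated. It also gives no pass rate for the check, so there is no planned figure to reproduce.

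**Formula.** With arm sizes n_j, K sensory-disturbance patients of whom O_j are in arm j, and p = K/N:

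chi-square = sum over arms of (O_j - n_j p)^2 / [n_j p (1 - p)].

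**Step 1: correct stratification.** Each complete block of eight puts two patients in every arm, and an incomplete last block puts 0 to 2 in each. Within a stratum, arm counts therefore differ by at most 2. Enumerating all incomplete-block outcomes at N = 90 gives a largest attainable chi-square of 5.63. One table that reaches it has K = 2 with both patients in one arm, so arms of 24, 22, 22 and 22. Then p(1 - p) = (2/90)(88/90) = 0.02173. The first arm contributes (2 - 0.5333)^2 / (24 x 0.02173) = 4.125. Each other arm contributes 0.4889^2 / (22 x 0.02173) = 0.5. The total is 5.625, below 7.815. At N = 88 the maximum is 6.14, also below. Correct assignment is never flagged.

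**Step 2: stratification ignored.** The null hypothesis holds, so rejection occurs at about the nominal rate. An exact calculation with arms of 23, 23, 22 and 22, and K from 5 to 63, gives a non-significant result with probability 94.8% to 96.9%.

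A constructed example shows how loose this is. Take K = 45 with sensory counts 16, 12, 10 and 7 in those arms. The terms are 4.5^2/5.75 = 3.522, 0.5^2/5.75 = 0.043, 1^2/5.5 = 0.182 and 4^2/5.5 = 2.909, total 6.656. The check passes, yet a spread of 16 - 7 = 9 is impossible under correct blocks, where the limit is 2.

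**Step 3: simulation.** N = 90, 10,000 to 20,000 trials per case. Ranges cover the three assumed prevalences and repeated runs.

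| How assignment was carried out | Chi-square p < 0.05 | Arms in a stratum differ by more than 2 |
|---|---|---|
| Stratified blocks of eight, correct | 0% | 0% |
| Simple randomisation | 4.7-5.0% | 99.6-99.9% |
| One unstratified list, blocks of eight | 4.7-5.5% | 90-93% |
| 10% of patients from the wrong list | 0.01-0.08% | 74-76% |
| 20% from the wrong list | 0.6-1.1% | 86-88% |
| 30% from the wrong list | 2.5-3.0% | 89-92% |

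At an assumed prevalence of 10%, the 20% wrong-list case is flagged by chi-square about 2% of the time (1 - 0.9786).

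**Step 4: limits of the count check.** The bound of 2 applies only to everyone randomised. If stratification is perfect but 2, 5 or 9 patients are lost at random before counting, the bound is broken in about 17%, 41-42% and 64% of trials. It also weakens when a stratum is small: at 10% prevalence, the sensory stratum alone stays within 2 in about 43% of trials run from one unstratified list. It is a screen; the record-by-record comparison supplies the evidence.

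**The case against.** **The test is inferred.** The sentence promises a comparison of frequencies and names neither a test nor a threshold. That is correct. Chi-square at 5% comes from the neighbouring statements, and a plain comparison of counts would also satisfy the wording. It remains the natural reading, because no other categorical method is named. The complaint is not that detail has been left to an analysis plan: the protocol itself says what this comparison will establish.

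**The check is not empty.** A reader might infer that it says nothing, or that it misses at least 95% of every kind of failure. Neither is supported. Simulated flag rates reach about 5.5% even when allocation stays random. Allocation tied to sensory status can also be detected: with an assumed steer of 40/20/20/20 for sensory patients and 10/30/30/30 for the others, chi-square rejected in 70-82% of trials at 30-70% prevalence. The protocol gives no sign that such steering is expected, but it would be improper assignment and the test could show it.

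**The route to error is not documented.** A reader might infer that the practitioner chooses between two envelope stacks and could take the wrong one. Section 2.5 does not say so; the coordinator who conducts the stratified randomisation may select the stratum. The wrong-list rows above are assumed scenarios.

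**Errors might surface anyway.** Opened envelopes are kept (Section 2.5), a coordinator compares case report forms with source documents (Section 2.14), and unequal subgroup arms would be visible in the tabulated frequencies. This is partial mitigation, since Section 2.14 does not mention the randomisation list.

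**The consequence is small.** No estimate depends on this check. That stands and sets the weight of the point.

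**Conclusion.** The point holds as a minor one. On the natural reading of Section 2.11, correct stratification passes always and omitted stratification passes about 95% of the time. Assignment with 10-20% of patients from the wrong list passes about 99% of the time or more. A non-significant comparison therefore cannot carry the conclusion the protocol attaches to it.

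The omitted-stratification figure follows from the logic of the test and varies little with prevalence. The wrong-list figures rest on the assumed 30-70% prevalence and on errors occurring at random. All of them require allocation to remain random with respect to sensory status.

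A reader might infer that the primary result is at risk. It is not: Bang's blinding index in each group is calculated without reference to this check. What changes is only what the trial may claim about the conduct of its stratification.

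**What to change.** Replace the sentence in Section 2.11 with wording such as:

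> Correct stratified assignment will be verified by reconciling, for every randomised participant, the sensory stratum recorded before randomisation, the envelope code and sequence, and the group given, against the R-generated stratified list; mismatches will be listed. Among all randomised participants, before any withdrawals, arm counts within each stratum should differ by no more than 2 (blocks of eight). The frequency of sensory disturbance by group will be tabulated without a significance test.

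The cost is one changed sentence and the reconciliation of 90 records, using envelopes that are already retained and a coordinator who already checks case report forms against source documents. Any individual assignment errors found would have to be reported. No patients, visits or procedures are added.

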In most clinical studies in stroke patients, acupuncture treatment is usually applied to the paralyzed acupoint. However, the paralyzed limbs of stroke patients have complex patterns of muscle tone, muscle strength, and sensory abnormality [17], and there could be differences in the degree of sensitivity during stitching and the discomfort felt during acupuncture treatment compared to those in healthy individuals. Therefore, it is difficult to apply the validation results of sham acupuncture treatments, evaluated in healthy individuals, to stroke patients. However, there has been no study that has evaluated which type of sham acupuncture is suitable for a study population of stroke patients. In addition, even in acupuncture-related clinical trials involving similar stroke types, there are limitations to performing a meta-analysis because of the different types of sham acupuncture treatments used in each study.

In this study, we will evaluate the success rate of blindness and the posttreatment response to sham acupuncture treatments (three types) compared with verum acupuncture treatment in hemiplegic stroke patients. To assess the success blinding rate of various sham acupuncture treatments, a randomized, double-blinded (participants and evaluator), 4 group paralleled clinical trial will be conducted. Through this study, we aim to explore the most appropriate sham acupuncture tool for clinical research on stroke.

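### Randomisation is stratified by sensory disturbance, but the named outcome analyses carry no stratum term and the subgroup analysis covers only the disturbed stratum

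*Protocol article*

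**What the plan says.** Section 2.5 makes sensory status the only stratification factor: "The stratification is performed according to whether there is a sensory disturbance of the affected limb (1: no sensory disturbance; 2: sensory disturbance"). It adds that "Block lengths are eight", with equal allocation to the four arms.

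Section 2.11 sets out the analysis. The primary outcome is Bang's index in each group, with the shams compared with verum. The discomfort questions and the MASS index are compared by ANOVA. No stratum term or stratified estimate is named for either.

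Sensory status enters section 2.11 in two places. One is a between-group comparison of how often it occurs, as a check on the stratification. The other is the subgroup analysis: "In subgroup analysis, we will compare the values of primary and secondary outcomes in patients with sensory disturbances". The sentence after that defines the disturbed patients only. The undisturbed stratum, a between-stratum difference and an interaction are not mentioned, and the section rules out sensitivity analyses.

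The Introduction explains why stroke patients are studied: their paralysed limbs have "complex patterns of muscle tone, muscle strength, and sensory abnormality", which may change how needling is felt. On size, section 2.10 says "we decided to recruit at least 22 participants for each group and to recruit 90 stroke patients considering withdrawal during the trial", and gives no power calculation: "Therefore, we did not follow the general method for obtaining the sample size".

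**The concern.** A factor is normally chosen for stratification because it is expected to affect the outcome, and the Introduction gives a reason to expect that here. Two consequences follow.

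**The subgroup.** Comparing devices within the disturbed stratum shows how they rank in those patients, with few patients per arm. It does not show whether sensory disturbance changes a sham's performance. A non-significant comparison there, beside a different overall result, could be misread as effect modification when it reflects only small numbers.

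**The ANOVA.** Stratified randomisation removes between-stratum variation from the comparison of arms. An ANOVA without the stratum leaves that variation in the residual, so its standard errors are too large and power is lost. In a trial of about 22 per arm with no power calculation, that precision can be recovered at no cost.

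**Working it through.** **Inputs from the protocol article:** four arms, equal allocation, two strata, blocks of eight (section 2.5); at least 22 per arm, 90 in total (section 2.10); 5% significance level (section 2.11).

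**Assumed, because the article does not give them:** 30% to 70% with sensory disturbance; stratum explaining 10% to 20% of outcome variance; index of 0; no do-not-know answers unless stated.

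**The plan's own figure.** 4 × 22 = 88, so 90 leaves 2 patients (2/90 = 2.2%) for withdrawal. The figure reproduces; no power-based figure is stated.

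**Precision in the disturbed stratum.** With n patients, the 95% half-width of the index is 1.96 × √(1/n), on a scale from -1 to 1.
- 30% of 22 = 6.6: 1.96/√6.6 = 0.76
- 50% of 22 = 11: 1.96/√11 = 0.59
- 70% of 22 = 15.4: 1.96/√15.4 = 0.50

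**Precision of the missing contrast.** For one device, disturbed minus undisturbed, the half-width is 1.96 × √(1/n_d + 1/n_u).
- 11 and 11: 1.96 × √(0.0909 + 0.0909) = 0.84
- 6.6 and 15.4, in either order: 1.96 × √(0.1515 + 0.0649) = 0.91

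If 30% answer do not know, the variance falls to 0.7 and the half-width to about 0.70 to 0.76. Without such answers, the difference detectable with 80% power is (1.96 + 0.84) times the same root, about 1.2 to 1.3.

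**Cost of leaving the stratum out of the ANOVA.** The ratio of unadjusted to adjusted standard error is 1/√(1 − R²).
- R² = 0.10: 1/√0.90 = 1.05
- R² = 0.20: 1/√0.80 = 1.12

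A simulation checked the direction: 88 patients, 44 per stratum, blocks of eight, normal errors, 4,000 runs per setting, and a 0.9 SD shift in one arm for power.

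| Assumed stratum effect | Type I error, unadjusted | Type I error, adjusted | Power, unadjusted | Power, adjusted |
|---|---|---|---|---|
| 0 | 5.8% | 5.8% | 87.0% | 87.0% |
| 0.5 SD | 4.8% | 5.8% | 83.8% | 86.2% |
| 1.0 SD | 2.4% | 4.9% | 77.8% | 87.0% |
| 1.5 SD | 0.9% | 4.7% | 63.9% | 85.8% |

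With equal strata, a 1 SD effect corresponds to R² = 0.25/1.25 = 0.20, the upper case above. With no stratum effect both tests have an exact level of 5%, so 5.8% is simulation error (Monte Carlo standard error √(0.05 × 0.95/4000) = 0.3 percentage points).

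**Primary index.** Each block of eight holds two places per arm, so within a stratum the arms differ by at most two patients at allocation. Stratum shares are therefore nearly equal across arms, and a stratum-weighted index would be close to the crude one.

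**The case against.** **The strata are used.** A reader might infer that no analysis uses the strata. Section 2.11 does not support that: it has the balance check, and its subgroup is itself one of the two strata. What stands is narrower. No primary or secondary outcome analysis is stated to adjust for the stratum, and only one stratum is analysed separately.

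**The ANOVA may yet be adjusted.** The text does not call it one-way or unadjusted, and covariates are commonly settled in an analysis plan, which is not shown. This makes adjustment the weaker half of the point. It does not touch the subgroup, whose restriction to disturbed patients is stated in the text.

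**Effect modification is not an objective.** A reader might infer that the trial cannot answer the question that motivated it. That goes too far. Sections 2.1 and 2.11 ask which sham is most suitable, or feels most like verum, in stroke patients, and the four-arm comparison addresses that. The Introduction contrasts stroke patients with healthy people and lists sensory abnormality beside muscle tone and strength. Asking which device does best in disturbed patients is also a legitimate question, and the plan nowhere says it will infer effect modification from it. Still, sensory status was chosen as the sole stratification factor, and the subgroup as specified cannot say whether it matters.

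**The contrast would be imprecise.** This is correct, and is why it should be exploratory. An interval that shows how little is known is still more informative than one stratum alone.

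**Conclusion.** The point holds as a limited weakness in the analysis wording. The disturbed-only subgroup gives no estimate of how a sham's performance differs by sensory status; that follows from the text and needs no assumption. The missing stratum term costs precision on the secondary outcomes only if sensory status affects them. The 5% to 12% wider standard errors rest on an assumed 10% to 20% of variance explained, and with no stratum effect nothing is lost.

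A reader might also infer that ignoring the stratum inflates type I error. It does the opposite: at a 1 SD stratum effect the unadjusted test rejects about 2.4% of the time at a nominal 5%.

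Reporting both strata would not make this a trial of effect modification. At about 22 per arm, the index contrast per device has a half-width of about 0.84 to 0.91 under the stated assumptions, and remains descriptive.

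**What to change.** Change section 2.11 as follows.

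1. **Scored secondary outcomes** (intensity, duration, MASS): include the sensory stratum used at randomisation as a factor in the ANOVA, and report sham-minus-verum differences adjusted for it.
2. **Yes/no discomfort items:** use a stratum-adjusted binary method, such as Mantel-Haenszel or logistic regression with the stratum as a term. A two-way ANOVA does not suit these items.
3. **Subgroup analysis:** replace the disturbed-only comparison with primary and secondary outcomes by device in both strata, giving the between-stratum difference (device-by-stratum interaction) with its 95% confidence interval.
4. **Interpretation:** label the stratum comparison exploratory, and state that no claim of effect modification will be made from one stratum alone.
5. **Primary index:** weighting by stratum is optional, since it should nearly equal the crude index.

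The cost is wording and a few extra table rows. The stratum is already recorded for every randomised patient, and no extra patients or measurements are needed.

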### 2.12. Quality Control

For quality control, we will conduct a number of simulations for our colleagues and volunteers before the start of the study. All practitioners will conduct the study according to the standard operating procedure (SOP) of the study. During the course of the study, regular meetings will be held to discuss issues raised by investigators or participants, the need to improve protocols, the side effects, and participant recruitment.

### 2.13. Data Management

Information obtained from each participant will be recorded on a paper document case report form (CRF). The collected information will then be entered into an SPSS file for future statistical analyses with coding. All of the above information will be stored in the confidential computer of the Stroke Center of Kyung Hee University Korean Medicine Hospital. This confidential computer will be managed by the Stroke Center of Kyung Hee University Korean Medicine Hospital. To protect personal information, all participants' full name and resident registration numbers etc. will not be disclosed and a unique identifier number given during the trial will be used to identify participants. All the participants will be informed that the clinical data in this trial will be stored in a confidential computer and will be discarded after the end of the trial. The written consents will be stored by the principal investigator's office in the Stroke Center of Kyung Hee University Korean Medicine Hospital.

